### **2.6.3 Diagnosis of hypertension**

The guideline defined hypertension in children and adolescents as systolic BP (SBP) or diastolic BP (DBP) or both SBP and DBP, which is, on repeated measurement, at or above the 95th percentile for age, sex and height. BP between the 90th and 95th percentile in childhood was designated "prehypertensive".

It further recommended that

1. “BP should be measured in the right arm with an appropriate cuff size(Flynn et al., 2017).
2. Appropriate steps should be taken to ensure the child is comfortable and still for at least 5 minutes prior to measurement.
3. Home BP measurements may help monitor hypertensives but not diagnose new cases.
4. Although measurement with an automatic BP cuff (oscillation device) may be used to screen for elevated BP in the primary care setting, it should be repeated with auscultation if the BP reading is elevated.
5. If an auscultated BP measurement is elevated despite correct measurement technique, it should be repeated two more times at the same visit and the average of the last two auscultatory readings used as a final BP. The degree of elevation should be assessed based on this average with reference to normative BP values for age, sex and height and the revised hypertensive categories as outlined in Figure 2A (Flynn et al., 2017).
6. A diagnosis of paediatric hypertension can be made if the BP remains at or above stage 1 hypertension on three separate clinic visits (Flynn et al., 2017). The timeline for these follow-up BP assessments is as outlined in figure 2A.
7. Compared to adults, their report gave no strict BP cut-off for a hypertensive crisis in children. However, it stated that severe hypertension warranting assessment in the emergency department depends on clinical symptoms, including irritability, headache, oedema, visual changes, or severe abdominal pain(Chandar & Zilleruelo, 2012; N. H. Patel et al., 2012; Stein & Ferguson, 2016).
8. Due to its superiority over isolated BP measurement in diagnosing hypertension and its ability to identify some secondary causes of hypertension, ambulatory blood pressure monitoring (ABPM) was recommended for screening or in confirming the diagnosis of hypertension if
   1. BP remains in the elevated BP category for ≥1 year
   2. BP remains in stage 1 hypertension category over three successive visits.
   3. The patient has high-risk conditions for hypertension (i.e., CKD, diabetes, obesity, or prematurity)

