### **2.6.4 Investigating the aetiology of hypertension**

Because children and adolescents have a higher prevalence of secondary hypertension than the adult population (Falkner & Daniels, 2004), the guideline recommends a thorough screen for causative factors once a diagnosis of hypertension is made. This assessment should include a thorough perinatal, nutritional, physical activity, psychosocial, medical and family history. It should be followed by a complete physical examination to help provide clues to potential secondary causes of hypertension and to assess possible end-organ damage. It should include assessing the BMI, checking BP in multiple limbs to diagnose coarctation of the aorta, and other assessments based on the clinical history. To detect underlying secondary causes, laboratory evaluation of newly diagnosed children is recommended. Assessments for renal, endocrine and other conditions suggested by history and physical examination is also recommended. Clinicians are encouraged to screen for conditions that are likely to increase stress, including depression, anxiety, trauma, or bullying(Flynn et al., 2017). Additional recommended assessments include those for target organ damage. These include assessments for

1. “Central arterial stiffness using pulse wave velocity, cardio-ankle vascular index, carotid intima-media thickness and flow-mediated dilatation.
2. left ventricular hypertrophy using electrocardiogram or echocardiography
3. Renal and renovascular disease using renal ultrasound or CT scan, microalbuminuria and other biochemical tests, including serum uric acid.” (Flynn et al., 2017)

Beginning with the history, topics that should be addressed include the child's perinatal course, diet, exercise, obesity, medications, and family history. Social history warrants particular attention as family income, parental education, poor sleep, and a lack of physical activity are independent risk factors for increased BP among children and adolescents (Y. Shi et al., 2012).

A comprehensive physical examination should then be performed, covering each system involved in any differential diagnosis considered. Electrolytes, creatinine, lipid profile, blood urea nitrogen, and urinalysis are to be done for all children and adolescents with hypertension(Flynn et al., 2017).

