### **3.3.9 Outcomes**

#### **a. Primary outcomes**

The primary outcome will be the effect of the intervention on healthcare workers’ adherence to the guideline. It will assess adherence to recommendations on the

1. frequency of screening
2. Detection of elevated or high BP,
3. Investigation of high BP and
4. Management of elevated or high BP.

These will be assessed using a data extraction tool based on the HIV client care booklet. The tool will extract the data from the client care records of adolescents who received care within the period of interest. At baseline, it will assess the records of 20 randomly selected adolescents who received care at the facility six months prior to the assessment and extract the data from their most recent visit. At follow up, data will be extracted from the most recent visit of 20 randomly selected adolescents who received care at the facility after the intervention commenced.

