**DATA EXTRACTION FORM**

| **Name of reviewer:……………………………………. Date:………………….** | | | |
| --- | --- | --- | --- |
| **Demographic characteristics** | | | |
| **Question No.** | **Variable** | **Variable code** | **Values** |
| 1) | Folder ID | FID | ………………….. |
| 2) | Study ID | SID | …………………. |
| 3) | District/Municipality | AREA | ………………….. |
| 4) | Facility | FAC | ………………….. |
| 5) | Date of data collection | DATE | dd-mm-yyyy………………………. |
| 6) | Sex | SEX | 0-Female  1-Male |
| 7) | Age (years) | AGE | ……………………………. |
|  |  |  |  |
| 8) | Occupation | OCC | ………………………………. |
| 9) | Highest educational level | EDUC | 1-No formal education  2-Primary school  3-High school  4-Tertiary |
| 10) | Marital status | MSTAT | 1-Single  2-Married  3-co-habitting |
| 11) | Religion | REL | 1-Christian  2-Muslim  3-Other (specify) |
| **Section II – Clinical characteristics** | | | |
| **12** | Date of HIV diagnosis | DD_HIV | dd-mm-yyyy………………………. |
| **13** | Age at HIV diagnosis | **AD_HIV** | ………………….years |
| **14** | HIV Type |  | 1-I 2-II 3-I & II |
| 15 | Weight at baseline | WT_BASE | ……………………………(Kg) |
| 16 | Weight at end line | WT_END | ……………………………(Kg) |
| 17 | Height | HT | ……… (m) |
| 18 | Date of ART initiation | DAI | dd-mm-yyyy………………………. |
| 19 | Age at ART initiation | AAI | …………………………………. |
| 20 | WHO Stage at ART initiation | WSI | 1-1  2-2  3-3  4-4 |
| 21 | Current ART regimen | CAR | ----------------- |
| 21 | Previous ART Regimen | PAR | ……………………….    ………………………. |
| 22 | Viral load at baseline | VL_B | 1-Suppressed  2-Unsuppressed  3-None |
| 23 | Viral load at baseline | VL_B | 1-Suppressed  2-Unsuppressed  3-None |
| 24 | Systolic BP at last visit | SBP | 1………..  2.Not recorded |
| 25 | Diastolic BP at last visit | DBP | 1………..  2.Not recorded |
| 26 | Action taken on BP | BP_ACT | 1. None  2. Rechecked to confirm  3. Given appointment to recheck  4. Counselled on lifestyle  5. Referred |
| 26 | Smoking | SMK | Yes___ No___ Ex____  If Yes: Type___________  Number /day or week_______ |
| 28 | Alcohol use | ALC | Yes___ No___  If Yes (Check one):  Every day___ ≥ Once weekly ___ ≥ Once monthly___ |

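### The extraction form and one-visit rule support the BP-checked measure, but they cannot score investigation and score detection and management only in part

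*Protocol*

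**What the plan says.** Protocol section 3.3.9 a defines the primary outcome as the effect on adherence to guideline recommendations in four areas. The first two are "frequency of screening" and "Detection of elevated or high BP"; the others are investigation of high BP and management of elevated or high BP. All four are to be assessed with one tool based on the HIV client care booklet. At baseline the tool is applied to 20 randomly selected adolescents per facility seen in the preceding six months, to "extract the data from their most recent visit". At follow-up it again reads the most recent visit of 20 adolescents, now among those who received care after the intervention began.

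The Data Extraction Form in the appendix holds age, sex, height, systolic and diastolic BP at the last visit (or not recorded), and one field headed "Action taken on BP". That field has five options: none, rechecked, appointment to recheck, lifestyle counselling, referred. The only dates are those of data collection, HIV diagnosis and ART initiation. The only drug fields are the current and previous ART regimens.

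On diagnosis, section 2.6.3 says: "A diagnosis of paediatric hypertension can be made if the BP remains at or above stage 1 hypertension on three separate clinic visits". On work-up, section 2.6.4 says that "the guideline recommends a thorough screen for causative factors once a diagnosis of hypertension is made", and it lists laboratory tests for all with hypertension. Section 2.6.5 includes drug treatment, with listed indications, in management. On frequency, section 2.6.2 gives annual screening, more often for those with specific risks, while section 2.6.8 cites national HIV guidance to screen at every visit.

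**The concern.** The primary outcome has four parts, and the instrument meant to measure them has data items for only some. If the form goes to the field as it stands, investigation will have no data in either arm. An adolescent started on antihypertensive treatment could be recorded only under another action or as none. Whether staff recognised a raised reading could be inferred only from what they did next.

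The one-visit rule adds a second gap. Investigation follows diagnosis, and diagnosis as described needs three visits, so one visit does not show whether the work-up was due. An adherence proportion then has neither a numerator nor a defensible denominator.

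The form also lacks a visit date, so nobody can confirm afterwards that a visit fell in the six months before baseline, or after the intervention began.

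**Working it through.** **Step 1. The plan's own figure, and what it covers.** Inputs from section 3.3.5: 17% against 34%, two-sided 5%, power 80%, 20 adolescents per facility, ICC 0.05.

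- Individually randomised size per arm: n = [1.96·√(2·0.255·0.745) + 0.8416·√(0.17·0.83 + 0.34·0.66)]² / 0.17², just over 102, rounded up to 103.
- Design effect: 1 + (20 − 1)·0.05 = 1.95.
- 103 × 1.95 = 200.85 per arm, and 200.85 / 20 = 10.04 facilities.

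This agrees with the stated ten per arm. Normal-approximation power is 80.2% at 10 facilities per arm and 86.9% at the 12 to be recruited. The calculation concerns one binary item, BP screened at a visit, which is also hypothesis 1 in section 1.10. The form can score that item.

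**Step 2. The four components against the form.**

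| Component | Relevant form items | What can be scored |
| --- | --- | --- |
| Screening frequency | BP at last visit, or not recorded | Proportion of last visits with a BP, which matches the every-visit standard (2.6.8). Not an interval, so not the annual standard (2.6.2) |
| Detection | Age, sex, height, BP, action | The analyst can classify the reading. The worker's own classification is not recorded, and a three-visit diagnosis cannot be seen |
| Investigation | None | Nothing |
| Management | Action field | Recheck, recheck appointment, counselling and referral. Not drug treatment |

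**Step 3. Why the screening standard matters.** Assume, for illustration, that visits are independent and each has a 17% chance of a BP check. The chance of at least one check in a year is 1 − 0.83² = 31% with two visits and 1 − 0.83⁴ = 53% with four. The last-visit measure gives 17% in both cases. The same practice therefore scores very differently under the two standards.

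**Step 4. How many adolescents the later components rest on.** Each arm has 12 × 20 = 240 adolescents. Section 2.5.4 cites a hypertension prevalence of 10.5% in adolescents living with HIV. Section 2.4.1 cites 4.0% globally at ages 10 to 17. Neither is known to apply here, so both are assumptions.

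- At 10.5%: 240 × 0.105 = 25.2 per arm. With a BP recorded in 17% to 34% of them, 4.3 to 8.6 have a reading to act on.
- At 4.0%: 240 × 0.04 = 9.6 per arm, giving 1.6 to 3.3.

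Roughly 2 to 9 hypertensive adolescents per arm would therefore have a recorded BP at the visit read. Those with elevated BP below the hypertension threshold would add to the detection and management denominators.

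**Step 5. Other sources in the protocol.** The adolescent survey in section 3.3.9 b asks about BP checks, education on hypertension and preventive behaviour. It names neither investigations nor antihypertensive treatment, so it does not fill the gap.

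**The case against.** The best defence is that the measure that matters most is intact. Hypothesis 1 and the sample size both concern BP checked at a visit. The form records it, and the adolescent survey gives a cross-check by asking about the last clinical visit. This stands in full.

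A reader might infer that frequency of screening can never be read from one visit. The documents do not support that. Under the every-visit standard in section 2.6.8, which section 3.2.1 also uses for the survey's target behaviour, the share of sampled last visits with a BP is a valid facility-level measure. The difficulty arises only against the annual standard.

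A reader might also infer that nothing about management can be judged from one visit. That is too strong. Section 2.6.3 calls for repeat readings at the same visit when BP is raised, section 2.6.5 makes lifestyle change the first step, and section 2.6.7 covers referral. All of these can fall due at one visit and have a code in the action field.

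A third tempting inference is that the missing visit date will dilute the treatment effect through pre-intervention visits counted as follow-up. The documents give no misfiling rate. The follow-up sample is restricted to adolescents seen after the intervention began, so their most recent visit falls after that point if the rule is followed. What is lost is the means of checking this.

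The repeated row "Viral load at baseline", with its repeated code, is best treated as clerical. The form also repeats item numbers, and viral load is not a trial outcome.

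Finally, the tool is to be pre-tested (section 3.4.1) and programmed on tablets (budget table), so the form may change. That is a reason to correct it now. The form was also read from a PDF and ends at item 28; nothing after that point is shown.

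**Conclusion.** The point holds in limited form. Of the four primary components, investigation cannot be scored at all. Detection and management can be scored only in part, because the worker's classification and drug treatment are not captured. Screening frequency is scorable as BP checked at the last visit but not as an interval. A single visit cannot establish a three-visit diagnosis, so it does not show whether the work-up in section 2.6.4 was due. The baseline and post-intervention windows cannot be verified.

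The powered comparison of 17% with 34% is unaffected, and no sample-size figure changes. What is at risk is the claim to report adherence on all four components as the primary outcome. A statistical analysis plan could choose among components but could not supply uncollected fields.

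This conclusion assumes that the appendix form is the tool meant in section 3.3.9 a and that it has no further fields. The count of about 2 to 9 hypertensive adolescents per arm with a recorded BP also depends on the assumed prevalence and checking rates.

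**What to change.** Make section 3.3.9 a and the extraction form agree before the tablets are programmed, in one of two ways.

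1. **Complete the form.** Add visit date, recorded BP classification or diagnosis, investigations ordered and treatment started. Read all visits in the six-month window for the investigation and management items, and keep the most recent visit for the BP-checked outcome. The cost is slightly longer extraction per booklet, from the same records and with the same data collectors.
2. **Narrow the primary outcome.** Limit it to BP checked at the last visit, as in hypothesis 1 and the sample size, and make the other components descriptive. This adds no extraction work but gives up a primary claim on detection, investigation and management. A visit date is still worth adding to verify the windows.

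Under either option, reconcile the screening frequencies in sections 2.6.2 and 2.6.8 and state the one standard against which adherence is scored. Correct the repeated viral-load row in the same revision.

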### **3.3.4 Recruitment**

Recruitment into the study will be done at three levels: health facilities, health workers and adolescents living with HIV.

1. **Health facility recruitment**

The PI will invite potential participating clusters (i.e. health facilities) through their respective administrators to participate. In each consenting facility, the PI will identify a primary contact person for the research team.

1. **Clinical staff recruitment**

Once facilities are recruited, the PI will contact the focal persons to obtain details of potential clinical staff who may be interested in participation based on the inclusion and exclusion criteria. The potential participants will be engaged to discuss the study protocol. Those who express interest will be provided with a study invitation pack, including a letter of invitation, information sheet and consent form.

1. **Patient recruitment**

Using a random sequence provided by the study team, a random sample of 20 adolescents living with HIV per facility will be selected for baseline and end-line assessment. The consent of their caregivers will be sought, followed by the adolescents’ consent or assent as may be age-appropriate.

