### **3.3.5 Sample size**

This study is designed to detect a doubling (100%) of the proportion of adolescent visits that had BP screening done (conservatively calculated in STATA version 16 as an increase from 17% to 34%) between the intervention and control groups. It is based on the assumption of a 2-sided test with 80% power at a 5% significant level, cluster sizes of 20 adolescents and an intra-cluster correlation coefficient (ICC) of 0.05. Accordingly, two groups of ten (10) health facilities will be needed at the minimum. As this sample size estimation does not account for any potential loss to follow-up, we will recruit additional two facilities per arm (24 in total). Thus, a total of about 96 health workers (4 per facility) and about 480 adolescents living with HIV (20 per facility) will be enrolled in this study.

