#### **b.Secondary outcomes**

The secondary outcomes of the study will assess the effect of the intervention on the adolescents living with HIV at the intervention facility. A cross-sectional survey and physiological assessments will be conducted among 20 randomly selected adolescents per facility at baseline and six months after the intervention in both arms of the study.

1. **Cross-sectional Survey among Adolescents Living with HIV**

This survey will validate the data extracted from the records and confirm that the adolescents received the interventions. Data will be collected by face-to-face interviews using a structured questionnaire based on an adaption of the WHO STEPS Questionnaire for Chronic Disease Risk Factor Surveillance(WHO, 2012). The questionnaire will collect data on; socio-demographic characteristics, history of tobacco use and alcohol consumption, physical activity, diet and anthropometric measurements. In addition, data will be collected to assess the

- Number of clients who reported having their BPs checked during the last clinical visit
- Number of clients who reported being educated on hypertension and its risk reduction during the last clinical visit and
- The number of clients who reported adhering to any preventive measures (diet, physical activity) in the week prior to the interview.

Height and weight measurements of respondents will be taken with calibrated stadiometers and a weighing scale, respectively. All measurements will be taken using the US Centers for Disease Control and Prevention (CDC) standard procedure(CDC, 2014).

1. **Physiological Assessments**

These assessments will identify adolescents with normal blood pressure, masked hypertension, white coat hypertension, elevated BP and high BP as defined in the guideline for screening and managing hypertension among children and adolescents(Flynn et al., 2017). The assessment will also help identify those at risk of being hypertensive (having arterial stiffness). These will be achieved by measuring their office blood pressure, ambulatory blood pressure and cardio-ankle vascular index (arterial stiffness) as described below.

- **Office Blood pressure**

Participants’ blood pressure will be assessed as recommended in the guideline for screening and managing hypertension among children and adolescents(Flynn et al., 2017) and described in section **2.6.3.**

- **Ambulatory blood pressure measurement(ABPM)**

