## **3.6.4 Compensation**

Adolescent participants coming for follow up assessments outside their scheduled facility visits will have their transportation reimbursed.

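### The follow-up index visit for the primary outcome has no cut-off before the six-month study assessment, so a BP reading made by or because of the study could be scored as health-worker behaviour

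*Protocol*

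**What the plan says.** **Primary outcome.** Protocol 3.3.9a assesses adherence from client care records, covering screening, detection, investigation and management. For the second round it states: "At follow up, data will be extracted from the most recent visit of 20 randomly selected adolescents who received care at the facility after the" start of the intervention. It gives no end date for this window, no exclusion of study visits, and no order between record extraction and study measurement.

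**Study measurements.** Under 3.3.9b, 20 randomly selected adolescents per facility, in both arms, have office BP, 24-hour ambulatory BP and CAVI at baseline and six months. Their purpose is diagnostic: "These assessments will identify adolescents with normal blood pressure, masked hypertension, white coat hypertension, elevated BP and high BP", as defined in the guideline. The budget table places the record review at the same two time points.

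**Who is sampled.** Section 3.3.4 says "a random sample of 20 adolescents living with HIV per facility will be selected for baseline and end-line assessment". Section 3.3.6 gives each facility one random list of 20 for the baseline and end-line survey, 3.3.5 enrols about 480 adolescents, and the budget covers about 480 records. Section 3.3.9b adds that the survey is to validate the extracted records.

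**Where assessments take place.** Section 3.6.4 reimburses transport for "Adolescent participants coming for follow up assessments outside their scheduled facility visits".

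**The form.** The data extraction form records systolic and diastolic BP at the last visit, or that none was recorded, and the action taken. It has no field for the type of visit or for who took the reading.

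**The concern.** The outcome is meant to show whether facility staff check and act on BP in ordinary care. The study also checks BP itself, in both arms, at the time the follow-up records are read. If the latest visit is the assessment day, two opposite errors are possible: a study reading in the booklet looks like adherence, while a check that staff skip because the team is measuring looks like non-adherence. Nothing on the form separates either from routine care.

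If upward contamination were equal in the arms, both rates would rise and the difference would shrink. If it were unequal, the estimate could move in either direction. Unequal contamination is conceivable because staff know their arm (3.3.6d).

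**Working it through.** **1. Can the follow-up index visit be a study assessment?**
- End-line: yes, if the assessment coincides with a scheduled visit. Section 3.6.4 allows this by reimbursing only assessments outside such visits. The window in 3.3.9a stays open through that day.
- Baseline: no. Baseline assessment precedes the intervention, and the follow-up window opens after it started. The baseline assessment can act only indirectly, by making staff or adolescents more alert to BP.
- Baseline extraction looks back over the six months before the assessment, so it is better protected.

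**2. Are the samples the same?** Sections 3.3.4, 3.3.5, 3.3.6 and 3.3.9b and the budget together point to one set of 20 per facility, since validating a record against an interview needs the same person. No sentence says so.

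**3. Reproducing the planned size.** Inputs from 3.3.5: "conservatively calculated in STATA version 16 as an increase from 17% to 34"%, a "2-sided test with 80% power at a 5% significant level", "cluster sizes of 20 adolescents and an intra-cluster correlation coefficient (ICC) of 0.05".
- Design effect: 1 + (20 − 1) × 0.05 = 1.95.
- Individual n per arm, pooled variance: [1.960 × √(2 × 0.255 × 0.745) + 0.842 × √(0.17 × 0.83 + 0.34 × 0.66)]² / 0.17² = 102.0, which rounds up to 103. Unpooled: 99.3.
- Clusters per arm: 103 × 1.95 / 20 = 10.04 (9.95 before rounding n up); unpooled 99.3 × 1.95 / 20 = 9.68.

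This agrees with "two groups of ten (10) health facilities will be needed at the minimum". Power at 10 per arm is 80.2% (pooled). The plan's figure is not in dispute.

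**4. Illustration of size.** Let f be the share of index visits that would otherwise show no BP but carry a study-derived one. The documents give no value, so f is an assumption. With the same f in both arms, the observed rate is p + f(1 − p) and the difference is 0.17 × (1 − f). With 12 facilities per arm, the effective n per arm is 12 × 20 / 1.95 = 123.1.

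| f (assumed) | Control | Intervention | Difference | Power, pooled | Power, unpooled |
|---|---|---|---|---|---|
| 0 | 17.0% | 34.0% | 17.0 points | 86.9% | 87.7% |
| 5% | 21.2% | 37.3% | 16.2 points | 79.9% | 80.8% |
| 10% | 25.3% | 40.6% | 15.3 points | 72.6% | 73.5% |
| 20% | 33.6% | 47.2% | 13.6 points | 58.6% | 59.3% |

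Example for f = 10%: control 0.17 + 0.10 × 0.83 = 0.253; intervention 0.34 + 0.10 × 0.66 = 0.406. At f = 5%, power is back to about the planned 80%, so the gain from the two extra facilities per arm is used up. Those facilities were added to cover loss to follow-up.

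**5. Unequal contamination.** With a true 17% in both arms and f = 10% in the intervention arm only, the observed rates are 17.0% and 25.3%, a spurious difference of 8.3 points. With f = 10% in controls only and a true 17% v 34%, they are 25.3% and 34.0%, so the difference is halved to 8.7 points.

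The model covers upward contamination only. Skipped routine checks would lower recorded screening and are not in the table.

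**The case against.** The strongest objection is that few assessments may fall on scheduled visits. The budget pays transport for 480 adolescents at both rounds (20 × 480 × 2 = 19,200), which would cover a separate trip for everyone. The CAVI conditions also resemble a dedicated appointment: 8 to 10 a.m., a controlled room, and 24 hours without exercise or caffeine. This stands and lowers the likely size of the problem. The budget line may be a ceiling, however, and it is not a rule that keeps the two visits apart.

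Nor does any section say that study readings enter the client booklet; sections 3.4.1 and 3.6.2 describe study data forms and coded questionnaires. Section 3.3.9a can also be read as a fresh draw of records at follow-up. Both points stand as uncertainty: the protocol neither states nor excludes these routes.

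A reader might infer that baseline screening makes control rates rise materially. The text does not support that. The effect would be sensitisation only, and no feedback of study results to staff is described. The cited 10.5% hypertension prevalence in adolescents with HIV (2.5.4) also limits it: reaching f = 10% by this path alone would need about 0.10 / 0.105 = 95% of them to gain a recorded check because of the study. The guideline orientation given to all 24 facilities (3.3.8) is a more direct reason for control rates to rise.

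A reader might also conclude that the damage could not be undone. That is too strong, because the study holds its own readings and dates and could compare them with booklet entries.

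**Conclusion.** The point holds as an open route to bias, not as demonstrated bias. The follow-up index visit has no cut-off before the six-month assessment, the study measures BP in both arms at that time, the samples probably overlap, and the form cannot identify the source of a reading. It does not follow from the documents that study BP checks will count as adherence. That requires an assessment on a scheduled visit, together with either a study reading in the booklet or a change in staff behaviour on the day.

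The size is unknown. The fall from about 87-88% power to 80-81% or 73-74% rests on an assumed f of 5% or 10%, equal in both arms, with the planned 17% v 34%, 20 per facility and ICC 0.05. Equal upward contamination dilutes the difference; unequal contamination could inflate or reduce it. Because protection costs almost nothing, this is a free improvement rather than a fault in the design.

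**What to change.** In 3.3.9a:
- Define the index visit as the last routine clinic visit before the date of that round's study assessment, within the relevant window.
- Exclude any BP taken by, or at the request of, the study team.
- State that study readings are kept on study forms only.
- State whether the record-review and assessment samples are the same adolescents.

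On the data extraction form, add visit type (routine or study) and who measured the BP.

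The cost is a few sentences and two form fields, with no extra participants, visits or records. These must be in place before end-line extraction.

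A separate record sample of adolescents not assessed at baseline is not needed. It would require up to 480 more records if validation is kept, about 480 / 20 = 24 collector-days at the budgeted rate, and would still leave any sensitisation of staff in place.
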